## **8.5 Trial management**

### **8.5.1 Monitoring**

The Mereva CTU and CCC will coordinate all study activities of the Project Team. This includes in particular to:

- Set up and monitor workflows, timelines, milestones and tracking tools;
- Conduct regular team meetings to discuss project status, activities, and address issues;
- Maintain daily contact with principal investigators, sponsor and clinical sites;
- Provide status reports to principal investigator, DSMB, and SAB;
- Support the study sites with study related questions;
- Ensure that study drug is being stored, dispensed, and accounted for according to specifications;
- Check the completeness of patient records, the accuracy of entries in the database, the adherence to the protocol, SOPs and to Good Clinical Practice. Monitoring standards require full verification for the presence of informed consent, adherence to the inclusion/exclusion criteria, documentation of serious adverse events (SAEs), and the recording of data that will be used for all primary and safety variables.

The investigator must give the CCC access to all relevant source documents to confirm their consistency with the CRF and database entries. For this particular trial, some documents filed in within the isolation ward will have to be destroyed in order to avoid contamination. These documents will be scanned or photographed prior to destruction.

Investigators at each clinical site will keep a hard copy of the Trial Master File (TMF), containing all essential technical (protocol, SOPs, etc.), and regulatory (insurance, IRB approvals, task delegation descriptions, bio-sketches, agreements, etc.) trial documents. The country CPM will be responsible for checking that the files containing the hard copy of the TMF documents at each trial clinic and at the CCC are up-to-date. All TMF documents will also be made available online to investigators on a private website (“eTMF”). The international CPM will be responsible for routinely updating the documentation on the trial website.

### **8.5.2 Data management**

The Mereva CTU will develop by December 1st, 2014:

A case report form (CRF): data will be collected on hard copy CRF in the EVD center. It will then be scanned or photographed prior to destruction. The medical investigator or his/her designated representative will be responsible for filling out the forms.

A database: data will be entered online in a system that will ensure data encryption, restricted access to the database, daily back-up, and tracking of edits.

A Data Management Plan (DMP) and Data Validation Plan (DVP), including the quality control process to ensure completeness, validity, consistency, timeliness and accuracy.

Training will be provided to all members of the study team involved in data collection data entry, data check and monitoring.

The Mereva CTU data managing team will conduct data review and handle queries on a weekly basis, and reconcile the safety database with the clinical database.

### **8.5.3 Pharmacovigilance and safety management**

Due to the international standard procedures for the prevention of EBOV transmission, body fluid collection will be limited to the bare minimum and tests such as X-ray or electrocardiogram will not be doable.

The following events will be defined as SAE, provided they occur after the first drug administration:

- death or life-threatening events,
- prolonged hospitalization, defined of a patients aggravation following improvement,
- grade 4 CTAE adverse events,
- grade 3 CTAE adverse event of special interest (rash, jaundice, clinical suspicion of anemia, petechiae, external bleeding, bradycardia, tachycardia, arrhythmia),
- and any events considered as medically important by the investigator.

Deaths will be reported to the sponsor and to the DSMB on a daily basis; SAE other than deaths will be reported to the sponsor and to the DSMB on a weekly basis. In addition, the DSMB will receive the results of all biological tests as soon as they are available.

## **8.6 Study medication manufacturing, packaging and shipping**

The Investigational Medicinal Product (favipiravir) will be manufactured according to GMP requirements by Toyama, Inc. Quality control testing has been performed to confirm that the study medication complies with all the defined quality standards for human use. Manufacturing records and a Certificate of Analysis will be provided to the trial investigators.

The study medication will be packaged in aluminum pouches including 240 tablets (24 tablets x 10).

A defined quantity of study medication will be shipped to the Japanese Embassy in Guinea in appropriate conditions. Relative humidity and temperature will be controlled during shipment.

Drugs will be picked up at the Embassy by a MSF team and transported to the trial central pharmacy in Gueckedou, where it will be kept in a safe place at controlled room temperature <30° C.

At the end of the trial, the unused and/or returned investigational medicinal products will remain at the disposal of the Guinean health authorities, who will be authorized to use it according to national procedures.

## **8.7 Trial surveillance**

### **8.7.1 Safety monitoring board**

An independent Data Safety Monitoring Board (DSMB) of seven external experts will oversee the trial, with special attention to severe adverse events, mortality, and number of subjects needed. The DSMB members are pharmacologist, statistician, virologist, anthropologist, pediatrician, infectious diseases specialist and experienced lead investigator in clinical trials in developing countries (*see the list in Appendix 5*). They will help make decisions that require an independent assessment while the trial is underway. This includes:

- Premature discontinuation of the inclusion in group A1, A2 and/or C, because of futility or toxicity criteria are met (*see section 10*), or because external new fact lead to recommend such discontinuation;
- Other substantial changes to the protocol deemed to be necessary based on the trial data or on external new facts.

Intermediate analysis for futility will be prepared by the steering committee and interpreted by the DSMB.

The recommendations from the DSMB with all documentation sent from the sponsor to the DSMB will be circulated to three ethics committees after each session.

### **8.7.2 Steering Committee and Scientific Advisory Board**

The Steering Committee is composed of leading investigators in each field. They meet on a weekly basis (*see the list in Appendix 5*).

The trial Scientific Advisory Board (SAB) is composed of the members of the steering committee, external experts and representatives of the sponsor. The SAB meets before the beginning of the inclusion and then at least once a month until the end of the trial. The SAB guarantees that the trial remains scientifically relevant and that the methods used are appropriate, in light of the reports made by the investigators and of any external new facts. It decides about protocol amendments, and whether to open or close trial sites (*see the list in Appendix 5*).

## **9. Statistical analysis**

### **9.1 Mortality**

Mortality at Day-14 will be reported with its exact 95% confidence intervals (CI), overall, and separately by groups (A1, A2, C).

The analyses will be performed first using the intention to treat approach, including all patients with positive PCR who received at least one dose of favipiravir. In case of missing data for mortality at Day-14 patient will be considered dead.

A per protocol analysis will then be performed, including all patients who received the treatment until Day-9 or death.

In each group, we will conclude that favipiravir decreases mortality if the upper bound of the 95% CI does not include the observed pre-trial mortality in untreated patients with same duration of symptoms prior to trial initiation (*see section 6.3*).

In group A1, if the number of deaths is  $\leq 24$  (40%),  $\leq 19$  (32%),  $\leq 13$  (22%) or  $\leq 8$  (13%) out of 60 participants, the upper bound of the 95%CI will be  $\leq 55\%$ ,  $\leq 45\%$ ,  $\leq 35\%$  and  $\leq 25\%$ , respectively.

In group A2, if the number of deaths is  $\leq 54$  (45%),  $\leq 42$  (35%),  $\leq 31$  (26%),  $\leq 20$  (18%) out of 120 participants, the upper bound of the 95%CI will be  $\leq 55\%$ ,  $\leq 45\%$ ,  $\leq 35\%$  and  $\leq 25\%$ , respectively.

In group C, if the number of deaths is  $\leq 17$  (38%),  $\leq 13$  (29%),  $\leq 9$  (20%),  $\leq 5$  (11%) out of 45 participants, the upper bound of the 95%CI will be  $\leq 55\%$ ,  $\leq 45\%$ ,  $\leq 35\%$  and  $\leq 25\%$ , respectively.

### **9.2 Other outcomes**

Mortality by Day-14 with exact 95%CI will be reported according to the second group definition (AC1, AC2, YC). In each group, we will conclude that favipiravir decreases mortality if the upper bound of the 95% CI does not include the observed pre-trial mortality (30%, 85% and 70%, respectively) in untreated patients with same characteristics of symptoms prior to trial initiation (*see section 6.3*).

All the following outcomes will be reported overall and separately by the two group definitions (A1, A2, C or AC1, AC2, YC).

The evolution of EBOV plasma RNA and infectious loads between Day-0 and the end of follow up will be described in each patient. The numbers, proportions and exact 95% CI will be described for grade 3-4 adverse events; resistance mutations; and patients reaching criteria for cure at Day-30. The distribution (median, IQR, min-max) of initial and maximal viral load, time to maximal viral load and to undetectability, and rate of increase/decrease will be reported. The distribution of trough concentrations of favipiravir at each point and the inter- and intra-patient variability of concentrations will be described.

Factors associated with mortality by Day-14, cure at Day-30 and grade 3-4 clinical or biological adverse events (including time between first symptoms and treatment initiation, evolution of EBOV viral load, trough concentrations of favipiravir) will be studied.

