### 2.7 Treatment duration

The duration of the viremic period in patients with EVD is 10 days (Ksiazek *et al.* 1999). In addition, in severely affected patients, profound immunosuppression may occur early after the disease onset, and we do not know whether this would still be the case or not in patients receiving the antiviral. Therefore, we chose to provide favipiravir during 10 days, to ensure optimal probability of success. If the control of viremia occurs early and leads to substantial clinical improvement, shorter duration could be considered in further studies.

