### 8.3 Trial development and scheduled assessment

Once the trial is opened, all patients who attend the trial centers will be assessed for inclusion and non-inclusion criteria. Those who fulfill inclusion criteria will be informed and proposed to participate. Those who accept will be asked for informed consent.

- **Trial treatment:**

- Adults (groups A1 and A2): Day-0, H0: 2400 mg (12 tablets); H8: 2400 mg (12 tablets); H16: 1200 mg (6 tablets). Day-1 to Day-9: 1200 mg (6 tablets) bid.
- Children (group C): The loading dose (Day 0) and the dose from Day-1 to Day-9 will be adapted to the body weight (*see Table I*).

- **Other treatments:** From Day-0 to end of follow-up, all participants will receive the standard package of care, as defined by the care providers. This will be the object of a data collection, but will not be imposed by the protocol.
- **Blood collection** (see Tables 2 and 3):
  - Adults (groups A1 and A2): blood will be collected in 4 ml trial tubes during: (i) routine care venepuncture (Day-0, end of symptoms (EOS)+72h); (ii) additional trial venepuncture at: Day-2, Day-4, Day-13 and Day-30.
  - Children (group C): blood will be collected in 4 ml trial tubes during: (i) routine care venepuncture (Day-0, EOS+72h); (ii) additional trial venepuncture at Day-2, Day-4, Day-13 and Day-30.

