**Table 2: assessment schedule in adults**

|                     | Clinical examination | Favipiravir (mg) | Blood collection | Additional venepuncture** | Additional laboratory manipulation*** |
|---------------------|----------------------|------------------|------------------|---------------------------|---------------------------------------|
| Day-0               | x                    | 6000 ‡           | 1 RCT + 1 TT *   | No                        | Yes                                   |
| Day-1               | x                    | 1200 x 2         | No               | No                        | No                                    |
| Day-2               | x                    | 1200 x 2         | 1 TT *           | Yes                       | Yes                                   |
| Day-3               | x                    | 1200 x 2         | No               | No                        | No                                    |
| Day-4               | x                    | 1200 x 2         | 1 TT *           | Yes                       | Yes                                   |
| Day-5 to Day-9      | x                    | 1200 x 2         | No               | No                        | No                                    |
| Day-10 to discharge | x                    | No               | No               | No                        | No                                    |
| EOS+72h             | x                    | No               | 1 RCT + 1 TT *   | No                        | Yes                                   |
| Day-13              | x                    | No               | 1 RCT            | No                        | No                                    |
| Day-30              | x                    | No               | 1 TT *           | Yes                       | Yes                                   |

EOS: end of symptoms; ‡ H0: 2400 mg; H8: 2400 mg; H16: 1200 mg;

\* RCT: routine care tube; TT: trial tube (4 ml EDTA tubes); \*\* Venepuncture not included in routine care;

\*\*\* Tube centrifugation and cryoconservation.

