## 8.4 Biology

*In trial settings laboratories:*

- At Day-0, Day-2 Day-4, Day-13 the following tests will be done: qualitative PCR (Altona qualitative RT-PCR commercial kit); and biochemical tests (creatininemia and others tests according to local choice), if biochemical tests are doable in the laboratory.

- At Day-30 the following tests will be done: biochemical tests (creatininemia and others tests according to local choice) only if tests at Day-13 were abnormal.

- EDTA tubes will be decanted, and the serum will be divided into two aliquots of up to 1 ml. Aliquots will be frozen at -20 °C.

*Outside trial settings laboratories:* all trial samples will be centrifuged and frozen on the day of collection. They will be used for virological tests that are currently not available in Guinea and that need to be done in a Biosafety level 4 laboratory. Therefore, they will be shipped frozen to the Lyon-Mérieux BSL4 laboratory, using international standard procedures, including triple-layer packaging (collection tube, plastic waterproof boxes, special cartoon box with the international label for transport of Infectious Substances: UN6.2 class A, UN2814), and disinfection procedures for the outside of the tube and inside/outside of the box and of the cartoon. A Material Transfer Agreement will be obtained by the sponsor.

In the BSL4 laboratory, Quantitative RT-PCR will be performed using a standard real-time RT-PCR procedure and a set of synthetic RNA quantified external calibrators. The infectious load will be evaluated by determining the number of infectious viral particles using a standard procedure relying on serial dilutions of sera and infection of Vero cells. Evolution studies will rely on the analysis of the kinetics of viral subpopulations as determined using next-generation sequencing methods. In brief, a series of overlapping PCR products spanning the complete genome will be generated using a high fidelity amplification protocol and sequenced using the Ion Torrent NGS platform. After quality check and trimming primer sequences, complete genome sequences will be rebuilt and used for sub-population analysis.

The following tests will also be made in the Lyon-Mérieux BSL4 laboratory:

- Concentrations measurement will be made by HPLC using methods provided by the manufacturer of the drug.
- Uricemia
- Other biochemical tests: liver enzymes, creatininemia, natremia and kaliemia (expect if the tests have been made in the setting laboratory).

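### Time to undetectability is to be summarised by median, IQR and min-max, but adults have no fixed blood draw between Day-4 and Day-13, where most early-treated survivors would be expected to clear

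*Protocol*

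**What the plan says.** Section 9.2 commits to a specific summary. It states that "time to maximal viral load and to undetectability, and rate of increase/decrease will be reported", and it fixes the form of the report: "The distribution (median, IQR, min-max) of initial and maximal viral load, time to maximal viral load and to undetectability". Like the other outcomes in that section, it is reported overall and under both group definitions (A1, A2, C and AC1, AC2, YC).

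The sampling that feeds it is set in sections 8.3 and 8.4:

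- Adults have "additional trial venepuncture at: Day-2, Day-4, Day-13 and Day-30", plus "routine care venepuncture (Day-0, end of symptoms (EOS)+72h".
- On site, "At Day-0, Day-2 Day-4, Day-13 the following tests will be done: qualitative PCR".
- Table 2 shows no blood collection in adults over the second half of treatment: "Day-5 to Day-9 | x | 1200 x 2 | No".
- In children (Table 3) the EOS+72h draw falls back to Day-12.

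The text of 8.3 and Table 2 disagree on Day-13 in adults. The text lists an additional trial venepuncture, while the table shows a routine care tube only: "Day-13 | x | No | 1 RCT | No".

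On when clearance is expected, section 2.7 says: "The duration of the viremic period in patients with EVD is 10 days". Group A1 (section 6.2) receives its first dose at most 72 h after first symptoms.

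**The concern.** Time to undetectability is never observed exactly. It is known only to lie between the last positive and the first negative sample. When draws are two days apart this matters little. Here the spacing goes from 2 days to 9 days just after Day-4, and then to 17 days. If most patients clear inside the 9-day window, a median of first-negative dates mainly reports when blood was next taken. The EOS+72h draw does fall inside the window for some patients, but its date follows symptoms, so the recorded clearance date then depends on symptom timing as well as on virus.

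At stake is how a virological result is read. Evolution of viral load under treatment is a secondary objective (section 3), and section 2.7 says that early control of viremia could lead to shorter treatment being considered in further studies. A late-running clearance time would be a poor guide to that question.

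**Working it through.** The protocol gives no figure of its own to reproduce here, so the check is what the planned draws would return for assumed true clearance times.

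**Inputs from the protocol.** Fixed draws on Day-0, 2, 4, 13 and 30 (8.3). Gaps: 2 − 0 = 2, 4 − 2 = 2, 13 − 4 = 9, 30 − 13 = 17 days. Viremia 10 days (2.7). A1 delay from symptoms to first dose at most 3 days (6.2).

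**Assumptions.** The 10 days run from symptom onset and vary between patients with SD 1 to 3 days. Delay is uniform on 0-3 days in A1 and on 4-7 days in A2. All patients survive. Clearance is dated at the first negative sample.

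**Formula.** True clearance day T = (duration of viremia) − (delay). Recorded day = earliest draw on or after T.

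**Without variation.** Delays of 1, 2, 3, 4 and 5 days give T = Day-9, 8, 7, 6 and 5, all recorded as Day-13. A delay of 6 days gives T = Day-4, recorded correctly.

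**With variation, simulated.**

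| | A1 (delay 0-3) | A2 (delay 4-7) | A1 − A2 |
|---|---|---|---|
| True median | 10 − 1.5 = 8.5 | 10 − 5.5 = 4.5 | 4.0 |
| Share clearing between Day-4 and Day-13 | 85-100% | 56-64% | |
| Recorded median, fixed draws only | 13 (IQR 13-13) | 13 (IQR 4-13) | 0 |
| Recorded median, EOS+72h added, uniform on Day-5 to Day-13 | about 12.5 | about 7.1 | about 5.4 |

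The A1 excess is 13 − 8.5 = 4.5 days on fixed draws and 12.5 − 8.5 = 4.0 days with EOS+72h. The A2 excess with EOS+72h is 7.1 − 4.5 = 2.6 days.

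**Sensitivity to the EOS assumption.** Let EOS track clearance instead: true median Day-8, IQR 6.7-9.4; EOS on average 3 days before to 2 days after clearance, SD 1.5. Recorded medians are then 10.6 to 13, that is 2.6 to 5 days late, with 23-50% of patients placed exactly on Day-13.

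**Sensitivity to the A2 delay.** Section 6.2 sets no upper limit on delay in A2. With delays of 5-8 or 3-10 days (mean 6.5 in each) the true A2 median is 10 − 6.5 = Day-3.5, and the fixed draws record Day-4. The recorded contrast is 13 − 4 = 9 days against a true 8.5 − 3.5 = 5.

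**Schedule variants.** With the children's Day-12 fallback the gap is 12 − 4 = 8 days, and true medians of Day-7 to Day-10 are recorded as Day-12. If adults have no Day-13 trial tube, as Table 2 shows, and EOS+72h is ignored, the quantitative RNA result after Day-4 would first be available on Day-30.

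**The case against.** The strongest reply is that 9.2 never says clearance is dated at the first negative sample. Handling of events between visits is commonly left to the SAP, and an interval-censored estimate also has a median and quartiles. This stands in part: the size of the bias belongs to one dating rule. But 9.2 also fixes min-max, which needs one date per patient, and no dating rule recovers information from an unsampled window. Midpoint dating on fixed draws would put nearly all of A1 at (4 + 13)/2 = Day-8.5. That matches the assumed truth only because of the assumptions chosen, and the IQR would still collapse to a single point set by the calendar.

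It is also fair that sparse sampling is deliberate. Section 2.9 limits blood handling to protect staff, so the point gives no ground for more draws.

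Four stronger readings are tempting and are not supported:

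- *The schedule hides a real A1-A2 difference.* The zero contrast leaves out the scheduled EOS+72h draw. With that draw the contrast is about 5.4 days, and with other plausible A2 delays it is enlarged even on fixed draws. Even in the zero case the planned IQRs differ (13-13 against 4-13).
- *Patients whose symptoms end early are recorded as clearing earlier.* An early EOS draw that is still positive pushes the first negative to Day-13, so the effect can go either way.
- *On-site PCR fills the gap.* Section 8.4 puts it on Day-0, 2, 4 and 13, the same days as the fixed draws.
- *This is a main virological endpoint.* It is one of several descriptive summaries, and no test or decision rule uses it.

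**Conclusion.** The point holds as a minor one. The 9-day interval without a fixed adult draw, and the choice of median, IQR and min-max, are in the protocol. That most A1 survivors clear in that interval rests on reading the 10 days in 2.7 as counted from symptom onset; 2.7 does not say so, nor whether the figure applies under treatment. Under that reading, first-negative dating puts the A1 median about 4 days late (about Day-12.5 to Day-13 against Day-8.5), or 2.6 to 5 days late when EOS is assumed to track clearance around a true median of Day-8. The recorded A1-A2 contrast ranged from 0 to 9 days against true differences of 4 to 5, so neither its direction of error nor its size can be stated in general. Late presenters in A2 may clear by Day-4, where draws are two days apart, and are then little affected. All figures are for survivors; deaths before clearance are a separate matter. The primary mortality analysis and its conclusion are unaffected.

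**What to change.** Change section 9.2, or the SAP text that implements it, as follows, with no new samples:

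1. Treat time to undetectability as interval-censored between the last positive and the first negative sample, estimated by group.
2. Report the proportion undetectable at each fixed draw (Day-2, Day-4, Day-13, Day-30), in place of the median, IQR and min-max of first-negative dates.
3. Repeat the analysis leaving out the EOS+72h draw. Standard interval-censored estimators such as Turnbull's assume that draw times carry no information about clearance, and a symptom-timed draw may break that assumption.

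For step 2 the text of 8.3 and Table 2 must be reconciled on whether adults have a trial tube on Day-13.

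The cost is a few lines of wording and a modest amount of extra analysis. The price in reporting is a wide interval in place of a single median: without the EOS+72h draw, a nonparametric A1 median could probably be placed no more closely than between Day-4 and Day-13. That is what the planned samples can support.
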